**Surveys**

***Baseline survey***

All participants will complete the baseline survey on the online survey platform (Wen Juan Xing, https://www.wjx.cn) at the time of registration. The baseline survey asks questions about their sociodemographic characteristics and sexual behaviors. After completing the survey, participants will receive 20 RMB (approximately 3 USD).

***Follow-up survey***

All participants in the two arms will be asked to complete a brief online survey in four weeks. The follow-up survey will collect information about HCV testing frequency, time, location, method and result(s), and sexual behaviors within four weeks. Participants will receive 30 RMB (approximately 4 USD) for the follow-up survey.

***Cost data***

We will use a micro-costing approach to identify, measure and value costs associated with the trial arms. The perspective will be from the health provider. This will include the start-up costs (e.g., packaging, personnel training), consumables (HCV self-testing kits, standard of care testing supplies), capital costs (office equipment, building rental), and personnel costs. The time horizon will be the duration of the trial.

**Statistical methods**

All inferential tests will be two-sided and conducted at a significance level of *α*= 0.05 using SAS version 9.4 (SAS Institute, Cary, NC, USA). Baseline socio-demographic and behavioral characteristics will be presented separately by treatment arm and totaled across arms. Whenever feasible, data visualization will present individual-level data points as well as summary statistics.

***Sample size***

Sample size was calculated using Fisher’s exact test for two proportions using estimates from initial pilot study data (*n*=50 participants) in SAS version 9.4 (SAS Institute, Cary, NC, USA). Two of the 50 participants were not included in the estimates since they did not provide one-month follow-up data. In trial 1 (HIV-negative MSM), the HCV testing rate in the HCVST arm and in the SOC arm was 78.9% and 10.5%, respectively. In trial 2 (MSM living with HIV), the HCV testing rate in the HCVST arm was 40.0%, and no participants in the SOC arm received testing for HCV.

For sample size calculations, we assumed equal sample sizes in HCVST and SOC (i.e., 1:1 allocation ratio), 90% power, significance level of *α*= 0.05, two-sided testing, and 20% loss-to-follow-up (LTFU). The estimated required sample size for trial 1 (HIV-negative MSM) was *n*=17 in each arm (*n*=34 total). The estimated required sample size for trial 2 (MSM living with HIV) was *n*=27 in each arm (*n*=54 total).

Since the pilot study was relatively small (*n*=48 evaluable participants, 38 HIV-negative and 10 MSM living with HIV), it is possible that the estimated effect sizes were exaggerated. Since our resources allow, we plan to enroll a sample size of 42 in each arm (*n*=84 total) for trial 1 (HIV-negative MSM) and a sample size of 42 in each arm (*n*=84 total) for trial 2 (MSM living with HIV). Thus, each NGO will enroll 24 participants: *n*=12 to trial 1 (HIV-negative MSM) and *n*=12 to trial 2 (MSM living with HIV). With this sample size and assuming a 10% testing rate in the SOC, we will be 90% powered to detect a difference of approximately 32% or greater in the HCV testing rate between the HCVST and SOC arms.

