**Table S2. Sample size calculations**

|  | **HIV-negative MSM** | **MSM living with HIV** |
| --- | --- | --- |
| Proportion tested in HCVST | 0.79 (15/19) | 0.40 (2/5) |
| Proportion tested in SOC | 0.11 (2/19) | 0 (0/5) |
| Alpha | 0.05 | 0.05 |
| Power | 0.9 | 0.9 |
| Anticipated LTFU | 0.2 | 0.2 |
| Sample size in both arms  (With 20% LTFU) | 34 | 54 |

Abbreviations: Men who have sex with men (MSM), hepatitis C virus self-testing (HCVST), standard of care (SOC), loss-to-follow-up (LTFU).

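### The 90% power for a 32-point difference assumes all 42 men per arm are evaluable; under the protocol's own 20% loss it is about 80%

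*Protocol*

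**What the plan says.** The Sample size section gives the method, "Sample size was calculated using Fisher’s exact test for two proportions", and lists its assumptions: 1:1 allocation, 90% power, alpha 0.05, "two-sided testing, and 20% loss-to-follow-up (LTFU". From the pilot rates it obtains 17 per arm for trial 1 and 27 per arm for trial 2. Table S2 has a row headed "Anticipated LTFU" with the value 0.2 in both columns, and labels its totals of 34 and 54 as including that loss.

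The next paragraph grants that the pilot was small and may have exaggerated the effects. It therefore raises enrolment to 42 per arm in each trial. For that number, "assuming a 10% testing rate in the SOC", it states that "we will be 90% powered to detect a difference of approximately 32% or greater in the HCV testing rate" between the arms. This sentence does not mention loss to follow-up.

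**The concern.** The 42 per arm is a number to enrol, not a number expected to be evaluable. Coming straight after a paragraph that builds 20% loss into its sample sizes, the power sentence reads as if it did the same. If it does not, the protocol credits the design with more power than its own assumptions allow.

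This is the only power statement tied to the sample size actually chosen, and it covers both trials. Enrolment was raised because the pilot effects might be too large, so the detectable difference is the figure that tells a reader how much protection the larger sample buys.

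**Working it through.** **Inputs**

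- From Sample size: Fisher's exact test; 42 enrolled per arm, 1:1; standard-of-care rate 10%; difference about 32 points, so 42% v 10%; target power 90%; loss 20%.
- From Statistical methods and Table S2: two-sided alpha 0.05.
- Evaluable after loss: 42 × (1 − 0.20) = 33.6, so 33 or 34 per arm.

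**Method 1: exact power.** For n per arm, list every pair (a, b) of numbers tested and mark those where the two-sided Fisher p-value is at most 0.05. Power is the sum over the marked pairs of Bin(a; n, p1) × Bin(b; n, p2).

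**Method 2: arcsine approximation with continuity correction.** Power = Φ{ [2·arcsin√(p1 − 1/(2n)) − 2·arcsin√(p2 + 1/(2n))] × √(n/2) − 1.96 }.

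**Step 1. Reproduce the stated figure with no loss.** At n = 42, method 2 gives (1.3859 − 0.6822) × √21 − 1.96 = 1.265, so power is 89.7%; the difference detectable with 90% power is 32.2 points. Method 1 gives 91.0% and 31.4 points. The protocol's 90% for about 32 points is therefore the result for 42 evaluable men per arm.

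**Step 2. Check the other two sample sizes with the same approximation.**

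- Trial 1 (15/19 v 2/19): power is 89.1% at 12 and 92.0% at 13 per arm. 13 / 0.8 = 16.25, so 17.
- Trial 2 (2/5 v 0/5): power is 88.6% at 20 and 90.6% at 21 per arm. 21 / 0.8 = 26.25, so 27.

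One method thus yields all three protocol figures, with the 20% loss applied to the first two and left out of the third.

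**Step 3. Apply the 20% loss to the third, at 42% v 10%.**

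| Evaluable per arm | Fisher power, exact | Power, arcsine approximation | Difference for 90% power: exact / approximation |
| --- | --- | --- | --- |
| 42 (no loss) | 91.0% | 89.7% | 31.4 / 32.2 points |
| 34 (20% loss) | 81.7% | 81.1% | 36.4 / 36.8 points |
| 33 (20% loss) | 80.1% | 79.7% | 37.2 / 37.5 points |

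**Step 4. Vary the assumptions (exact Fisher power).**

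- 10% loss, about 38 per arm: 87.2%.
- 5% loss, about 40 per arm: 89.1%.
- Lost men kept in the analysis as not tested: the rates become 0.8 × 42% = 33.6% and 0.8 × 10% = 8%, with all 42 per arm. Power is 80.0%.
- Trial 2 if its pilot self-testing rate of 40% meets the assumed 10% under standard of care: 87.4% with no loss, 76.8% at 34 and 75.0% at 33 per arm.

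**The case against.** The sentence is conditional on the enrolled number and does not claim to include loss; at 42 per arm the figure is right. The 42 was not derived from 32 points but chosen because resources allowed it, and it exceeds the loss-inflated 17 and 27. At the pilot rates, Fisher power with 33 per arm is above 99% in both trials. All of this stands, and it limits the consequence: neither trial is underpowered for the effect the pilot saw. It does not make the sentence consistent with the loss assumption in the paragraph before it.

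The figure of 80% also depends on the full 20% loss, whereas the missing-data section expects less than that, and the pilot lost 2 of 50 (4%). This too is fair. But 20% is the protocol's planning value, and even a 10% loss leaves power below 90%.

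The planned analysis is a difference in proportions, not Fisher's test. With 34 per arm, the pooled chi-square test has about 87% to 89% power and the unpooled Wald test about 90%. These are not the stated sample-size method, and they do not give 17 and 27 for the pilot rates. The unpooled Wald test, for example, gives 6 and 16 evaluable per arm, which is 8 and 20 after inflation.

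At 11% to 20% missing, the main analysis would use multiple imputation rather than complete cases, and a man lost to the survey may still have sent a photo. The complete-case count of 33 or 34 is thus a planning approximation. The protocol's own inflation of 17 and 27 rests on the same approximation.

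The 40% v 10% scenario for trial 2 combines rates that the protocol does not pair, and its 30 points fall short of 32 even without loss. It illustrates the margin and is not evidence of the error.

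**Conclusion.** The concern holds. The power statement for the chosen sample size omits the loss that the protocol assumes for its other calculations. With Fisher's exact test, two-sided 0.05, a 10% standard-of-care rate and 20% loss in each arm, power for 32 points is 80% to 82%, not 90%. The difference detectable with 90% power is 36 to 37 points, about 5 more than stated. With less loss, or with a less conservative test, the shortfall is smaller. The sentence is wrong as written, but the enrolment target need not change.

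**What to change.** Replace the last sentence of the Sample size section with one that carries the loss, for example: with 42 enrolled per arm and 20% loss (33 to 34 evaluable per arm), a 10% testing rate under standard of care and Fisher's exact test at two-sided 0.05, each trial has 90% power for a difference of about 37 percentage points and about 80% power for 32 percentage points. Alternatively, keep the 32-point figure and state that it assumes no loss, with the after-loss figure beside it. Writing percentage points also removes any doubt about whether the difference is absolute.

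The cost is one sentence and a less favourable number. No participants are added, and the design and analysis stay as they are.

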**Table S2. Sample size calculations**

|  | **HIV-negative MSM** | **MSM living with HIV** |
| --- | --- | --- |
| Proportion tested in HCVST | 0.79 (15/19) | 0.40 (2/5) |
| Proportion tested in SOC | 0.11 (2/19) | 0 (0/5) |
| Alpha | 0.05 | 0.05 |
| Power | 0.9 | 0.9 |
| Anticipated LTFU | 0.2 | 0.2 |
| Sample size in both arms  (With 20% LTFU) | 34 | 54 |

Abbreviations: Men who have sex with men (MSM), hepatitis C virus self-testing (HCVST), standard of care (SOC), loss-to-follow-up (LTFU).

***Analysis plan***

*Primary outcome*

The primary outcome of HCV testing rate (including facility testing and self-testing) within four weeks will be evaluated using a difference in proportions. We are interested in determining whether there is an overall difference in HCV testing rates between the arms. There may be differences in patient populations across provinces (NGOs), so we will adjust for NGO in the analysis if there is evidence of such differences. The appropriate approach for such an analysis will depend on the frequency of testing in each arm. A model-based approach that uses identity link and binomial family can be used to adjust for NGO if the frequencies are not too extreme (e.g., too few testers in SOC). Otherwise, a stratified test like Cochran–Mantel–Haenszel can be used to produce an adjusted *P*-value. We may also consider pooling data from NGOs that have low frequencies in the SOC arm (e.g., 0 or 1 testers) prior to adjusting for NGO.

*Secondary outcomes*

Secondary outcomes of testing rates for HIV, chlamydia, and gonorrhea will be also be evaluated as a difference in proportions using the methods described for the primary outcome.

*Economic evaluation*

We will estimate the total unit and incremental unit cost for each arm in two trials. All costs will be categorized as startup costs, fixed costs and variable costs in this study. Start-up costs refer to the cost which are incurred in the process of study beginning, including coordination of survey platforms. Fixed costs refer to the cost which cannot change with the number of participants during the whole trial period, including venue and equipment cost. Variable costs refer to the cost which are expenses that vary with the number of participants used, including HCVST kits, postage and other consumables. We will calculate all the costs for each arm, and then this cost will be divided by the number of MSM tested and the number of newly detected HCV cases in each study arm to calculate incremental unit costs. In addition, the univariate, multivariate and probabilistic sensitivity analyses from a decision tree model will be used to examine uncertainty.

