**Study setting and population**

Participants are eligible if they are born biologically male, age 18 years or above, having anal sex with other men, reporting not testing for HCV in the past year, reporting at least one of the following risk factors in the past year (condomless anal sex or STD diagnosed or injection drug use), plan to live in China for the next month and have a stable residence where they can securely receive a postal package. Participants are excluded if they are participating in similar clinical trials or other programs involving HCV testing or unwilling or unable to comply with all the requirements of the study. All enrolled participants will be divided into the two trials according to their HIV status. All participants will be recruited from seven MSM-led clinics run by MSM-focused community-based organizations(CBOs) in seven provinces located in different parts of China: East China (Shandong Province), [South China](https://en.wikipedia.org/wiki/South_Central_China) (Guangdong Province), [Northeast China](https://en.wikipedia.org/wiki/Northeast_China) (Liaoning Province), Northwest China (Qinghai Province), Central China (Hubei Province), Southwest China (Chongqing), and North China (Hebei Province). All the MSM-led clinics offer free HIV and syphilis testing and counseling for MSM. Staff at each CBO site also have rich experience in HIV/syphilis counseling and intervention. All the MSM living with HIV will be recruited offline and HIV-negative MSM will be recruited by half of the online and offline ratios through CBOs. All study sites will follow the same research procedure.

All participants will be asked to finish a baseline survey for eligibility screening through Wenjuanxing (an online survey platform belonging to Changsha Ranxing Information Technology Co., Ltd, China). Online informed consent will be obtained before the baseline survey by clicking on a “button” indicating that the participant has read the consent form and agrees to participate in this research.

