**Randomization and allocation**

All eligible individuals who complete the baseline survey and provide contact information will be assigned to one of the two arms in a 1:1 ratio using a randomized block design. A separate randomization procedure will be used for each NGO to generate 12 HCVST/SOC randomized assignments for trial 1 (HIV-negative MSM) and 12 HCVST/SOC randomized assignments for trial 2 (MSM living with HIV). The final randomization schedule will be generated by a statistician who is not involved in participant recruitment, using SAS version 9.4 (SAS Institute, Cary, NC, USA). Statisticians who analyze the data will be the only blinded people in this study.

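### NGO is the randomisation stratum, yet the primary analysis includes it only on unspecified evidence and picks the method from observed counts, with a fallback described as giving only a P-value

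*Protocol*

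**What the plan says.** Protocol, Randomization and allocation: men are "assigned to one of the two arms in a 1:1 ratio using a randomized block design", and "A separate randomization procedure will be used for each NGO". Each NGO's schedule holds 12 assignments for trial 1 and "12 HCVST/SOC randomized assignments for trial 2 (MSM living with HIV"). Under Study setting and population, men are "recruited from seven MSM-led clinics run by MSM-focused community-based organizations", so each trial has seven strata.

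Protocol, Analysis plan: the primary outcome, the proportion tested for HCV within four weeks, "will be evaluated using a difference in proportions". On NGO, the section first notes that patient populations may differ across provinces, then continues: "so we will adjust for NGO in the analysis if there is evidence of such differences". It does not say what counts as evidence, on which variable, or when it is judged.

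The adjusted method then depends on how often men in each arm tested. "A model-based approach that uses identity link and binomial family can be used to adjust for NGO" when the frequencies allow it. Otherwise a CMH-type test is to supply an adjusted P-value. NGOs with zero or one SOC tester may also be pooled before adjustment. The secondary outcomes of HIV, chlamydia and gonorrhoea testing follow the same rules.

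**The concern.** The design has already settled whether NGO belongs in the analysis: it defines the groups within which men were randomised. The plan reopens the question and leaves it to an undefined look at the data, with 12 men per NGO.

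Three things follow. Whether the stratum is respected may be a matter of chance. If it is dropped when NGOs do differ, the interval is wider than the design warrants. And because the adjusted method and any pooling are chosen from counts by arm, two analysts following the text could report different primary results. One of the permitted routes, as described, leaves the stated effect measure without an adjusted estimate or interval.

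**Working it through.** **1. The plan's own figures.** Sample size (Protocol, Sample size and Table S2) rests on Fisher's exact test without strata. With the arcsine approximation with continuity correction,

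power = Φ{√(2n)·[arcsin√(p_high − 1/2n) − arcsin√(p_low + 1/2n)] − 1.96}:

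- Trial 1, 15/19 v 2/19: n = 13 per arm gives 0.920; 13/0.8 = 16.25, so 17, as stated.
- Trial 2, 0.40 v 0: n = 21 gives 0.906; 21/0.8 = 26.25, so 27, as stated.
- 42 per arm, 0.10 v 0.42: 0.897, or 0.910 by exact enumeration, which fits the stated 90%.

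The plan states no figure for the interval.

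**2. Layout.** 7 NGOs × 12 = 84 men per trial, 42 per arm. I assume 6:6 within each NGO; the block size is not stated.

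**3. Why ignoring NGO can widen the interval.** The unstratified variance is [p0(1−p0) + p1(1−p1)]/42. At 0.10 v 0.42 this is (0.0900 + 0.2436)/42 = 0.00794, SE 0.089. Under randomisation within NGO the true variance is lower by (V0 + V1)/42, where V0 and V1 are the between-NGO variances of the true testing rates in each arm. If V0 = V1 = 0, nothing is lost.

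**4. Size.** The documents give no between-NGO variation, so I assume a range of SDs on the logit scale. The simulation has 60,000 trials per scenario. Evidence is assumed to be a chi-square test of outcome by NGO at p < 0.05. The stratified SE uses within-NGO variances with divisor 5 (six men less one). Results for 0.10 v 0.42:

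| NGO logit SD | 0 | 0.5 | 1 | 1.5 | 2 |
|---|---|---|---|---|---|
| NGO range, SOC | 0.10 | 0.04–0.18 | 0.02–0.28 | 0.00–0.36 | 0.00–0.44 |
| NGO range, HCVST | 0.42 | 0.24–0.61 | 0.12–0.77 | 0.05–0.87 | 0.02–0.93 |
| Unstratified SE ÷ true SE | 0.99 | 1.01 | 1.07 | 1.15 | 1.25 |
| 95% CI half-width, unstratified | 0.172 | 0.172 | 0.173 | 0.173 | 0.173 |
| 95% CI half-width, stratified | 0.174 | 0.170 | 0.160 | 0.149 | 0.138 |
| Trials with evidence found | 0.02 | 0.12 | 0.54 | 0.89 | 0.99 |
| Coverage, unstratified | 0.945 | 0.949 | 0.962 | 0.976 | 0.985 |
| Coverage, conditional rule | 0.945 | 0.947 | 0.948 | 0.946 | 0.942 |

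Other rates:

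- At the trial 1 pilot rates (0.105 v 0.789), the SE ratio is 0.98, 1.00, 1.04, 1.12 and 1.20 across the five SDs.
- At 0.02 v 0.40, close to the trial 2 pilot, it is 0.99, 1.01, 1.08, 1.17 and 1.27.
- At SD 1 evidence is found in 8% and 28% of trials respectively. The assumed test ignores arm, which makes it weak when the arms differ greatly; another test would give other percentages.
- Conditional-rule coverage is 0.920–0.948 and 0.938–0.950. The 0.920 occurs with no NGO differences and is the same without any stratification, so it belongs to the simple Wald interval and not to the rule.

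**5. No true effect.** At 10% in both arms, the unstratified test rejects in 5.7% (SD 0) down to 3.3% (SD 2) of trials, against 4.6–5.2% for CMH. With NGO rates of 10–50%, rejection is 4.1% unstratified, 4.9% CMH and 4.8% under the conditional rule.

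**6. Sparse cells.** With 10% SOC testing and six SOC men per NGO:

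- Expected testers: 6 × 0.10 = 0.6 per NGO.
- P(no tester) = 0.9^6 = 0.531. P(at least one of seven NGOs has none) = 1 − (1 − 0.531)^7 = 0.995.
- P(zero or one tester) = 0.531 + 6 × 0.10 × 0.9^5 = 0.531 + 0.354 = 0.886. Expected NGOs open to pooling: 7 × 0.886 = 6.2 of 7.

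So at the plan's own SOC rate, the fallback and the pooling option are the expected case, and pooling could undo nearly all the stratification. In trial 2 the pilot SOC count was 0/5.

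**The case against.** The strongest reply is that the plan does not prescribe an unstratified analysis when NGOs differ clearly; it says to adjust then. This stands, and it limits the size of the problem. With SOC rates of 0–33% and HCVST rates of 10–79% across NGOs (assumed), never stratifying gives an SE of 0.088 against a true 0.080–0.081. A reader might infer that the plan's intervals are simply too wide, or that it forfeits about 18% of the sample, since (0.0797/0.0881)² = 0.82. The documents do not support that. The figure costs a never-stratified analysis under strong invented heterogeneity. In that scenario the conditional rule, read as a chi-square test, triggers adjustment in 70% of trials, and its mean SE is 0.081 with coverage of 0.945–0.950. Power is 96% never stratified and 97% under either the conditional rule or constant stratification.

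A second reply is that the sentence speaks of differences in patient populations, which could mean baseline differences. That is a fair reading, so one cannot say that the decision to adjust must follow a look at outcomes. The choice of method and the pooling, however, explicitly use testing counts by arm.

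Third, the analysing statisticians are blinded. This limits deliberate choice, although pooling on SOC counts requires knowing which arm is SOC.

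Fourth, an analysis plan not shown may define the evidence. It could add a threshold, but the protocol would still make a design factor optional.

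**Conclusion.** The point holds as a mismatch between design and analysis, with an under-specified primary method. NGO is the stratum by design, its inclusion rests on undefined evidence that 12 men per NGO supply unreliably, and the adjusted method and pooling depend on observed counts. The likely fallback, as described, gives no adjusted difference or interval for an outcome defined as a difference in proportions.

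The numerical effect is modest and conservative. If NGOs differ and the unstratified analysis is used, its SE is too large by up to 1% at logit SD 0.5, 4–8% at SD 1 and 12–17% at SD 1.5. If they do not differ, it is not too large. Under a chi-square pre-test, overall coverage at 0.10 v 0.42 is 0.942–0.948. I claim neither type I error inflation nor a loss of sample. These sizes rest on the assumed NGO variation, the assumed pre-test and 6:6 balance. The mismatch itself rests only on the text. It should be corrected before analysis, but it does not threaten the trials' validity.

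**What to change.** In Protocol, Analysis plan, delete the condition on evidence, the choice of method by observed counts, and the pooling of NGOs. State instead that in each trial the primary and secondary testing-rate comparisons are always stratified by the seven NGOs, using one pre-specified method that tolerates zero cells and gives an interval. An example is the Mantel–Haenszel stratified risk difference with 95% CI, accompanied by the CMH P-value. Report the unstratified difference as supportive.

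Name a variance suited to small strata. A plug-in within-NGO variance with divisor 6 instead of 5 would be too small by a factor of 5/6, an SE factor of √(5/6) = 0.91.

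With 6:6 in every NGO the Mantel–Haenszel weights are all 6 × 6/12 = 3, so the point estimate equals the unstratified difference and only its standard error changes.

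The cost is one or two sentences and, if NGOs do not differ, about 1% in interval width (0.174/0.172 = 1.01). Sample size, data collection and participants are unaffected.

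### NGO adjustment of the primary outcome depends on outcome counts by arm, and with six SOC men per NGO the listed methods seldom give a seven-stratum adjusted risk difference with an interval

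*Protocol*

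**What the plan says.** **Design.** The Protocol (Randomization and allocation; Sample size) has seven NGOs. Each enrols 12 men into each trial, allocated 1:1 by a separate blocked randomization per NGO. That is six SOC and six HCVST men per NGO per trial, and 42 per arm.

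**Analysis.** The Analysis plan makes the difference in proportions the primary measure. Adjustment for NGO follows only if there is evidence that NGOs differ, and the approach is to depend on how often testing occurs in each arm. The first option is: "A model-based approach that uses identity link and binomial family can be used to adjust for NGO". It applies if frequencies are not too extreme, and too few SOC testers is the example of an extreme. Otherwise a stratified test such as CMH may supply an adjusted P-value. A further option is: "We may also consider pooling data from NGOs that have low frequencies in the SOC arm (e.g., 0 or 1 testers"). No cut-off is given for evidence of differences or for extreme frequencies.

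**Blinding.** Randomization and allocation states: "Statisticians who analyze the data will be the only blinded people in this study".

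**Expected rates.** For trial 1, "the HCV testing rate in the HCVST arm and in the SOC arm was 78.9% and 10.5%, respectively". For trial 2, "the HCV testing rate in the HCVST arm was 40.0%, and no participants in the SOC arm received testing for HCV". For the enrolled size, "assuming a 10% testing rate in the SOC, we will be 90% powered to detect a difference of approximately 32% or greater".

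**The concern.** The rates the Protocol itself expects put most NGO strata at zero or one SOC tester, and the listed methods cope badly with that.

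- An identity-link model with seven NGO terms must keep every fitted probability between 0 and 1. Strata without SOC testers push the fit onto the limit, where standard errors and Wald intervals are unreliable and convergence may fail.
- The pooling example would catch nearly every NGO, so it hardly separates sparse sites from the rest.
- The CMH fallback, as written, does not return the measure the plan has chosen.

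The route is settled by looking at outcome counts by arm. At stake are the validity of the primary interval and P-value, and freedom from a data-driven choice of method.

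**Working it through.** **1. The plan's own figures.** Inputs (Sample size; Table S2): 15/19 v 2/19 in trial 1, 2/5 v 0/5 in trial 2, and "90% power, significance level of *α*= 0.05, two-sided testing, and 20% loss-to-follow-up (LTFU"). The Walters approximation to Fisher's exact test is

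power = Φ{√(2n)·[arcsin√(p₁ − 1/(2n)) − arcsin√(p₀ + 1/(2n))] − 1.96}.

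- Trial 1: n = 13 per arm gives 92.0%; 13/0.8 = 16.25, so 17 per arm, 34 in total.
- Trial 2: n = 21 per arm gives 90.6%; 21/0.8 = 26.25, so 27 per arm, 54 in total.
- 42 per arm, 10% v 42%: 89.7% (91.0% by exact Fisher enumeration).

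All agree with the Protocol. The sample size is not in question.

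**2. How many NGOs the pooling example catches.** For X ~ Binomial(6, p), P(X ≤ 1) = (1−p)⁶ + 6p(1−p)⁵. At p = 0.10 this is 0.531 + 0.354 = 0.886.

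| SOC rate | P(0 or 1 of 6) | Expected NGOs of 7 | P(all seven) |
|---|---|---|---|
| 0% (trial 2 pilot) | 1.000 | 7.0 | 1.00 |
| 10% (planned) | 0.886 | 6.2 | 0.886⁷ = 0.43 |
| 10.5% (trial 1 pilot) | 0.875 | 6.1 | 0.39 |
| 20% | 0.655 | 4.6 | 0.05 |
| 30% | 0.420 | 2.9 | 0.002 |

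When all seven are pooled, one stratum is left and there is no NGO adjustment.

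**3. How often the identity-link fit reaches a boundary.** The model is p = aₖ for SOC and aₖ + d for HCVST, k = 1,…,7. In a stratum with no SOC testers and y HCVST testers, the slope of the log-likelihood at aₖ = 0 is y/d − (6−y)/(1−d) − 6. If it is not positive, the maximum lies at aₖ = 0.

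Take d = 0.32. For y = 3 the slope is 9.38 − 4.41 − 6 = −1.04 (boundary). For y = 4 it is 12.5 − 2.94 − 6 = 3.56 (interior). So a stratum with no SOC testers and at most three HCVST testers is on the boundary.

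- 10% v 42%: P(no SOC testers) = 0.9⁶ = 0.531 and P(y ≤ 3) = 0.792, so 0.421 per stratum. At least one of seven: 1 − 0.579⁷ = 0.98.
- 20% v 52%: 0.262 × 0.618 = 0.162 per stratum; 1 − 0.838⁷ = 0.71.

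This check holds d fixed. Simulations that estimate d by constrained maximum likelihood, with no true NGO differences, give 0.95–0.97 at 10% v 42%, about 0.98 at the trial 1 pilot rates, 1.00 at 0% v 40%, and 0.71 at 20% v 52%. Monte Carlo error is about one point. With 20% loss to follow-up, the 10–10.5% SOC scenarios give about 98%, with 6.4–6.5 NGOs flagged.

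**4. What pooling leaves.** In 500 simulated trials per scenario:

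| Rates | One stratum left | Two or more, interior fit | Two or more, boundary |
|---|---|---|---|
| 10% v 42% | 0.42 | 0.55 | 0.03 |
| 10.5% v 78.9% | 0.40 | 0.40 | 0.20 |
| 0% v 40% | 1.00 | 0 | 0 |

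**5. A stratified alternative.** The Mantel-Haenszel weight is n₁ₖn₀ₖ/(n₁ₖ + n₀ₖ) = 36/12 = 3 in every complete stratum. The estimate is Σ3(y₁ₖ − y₀ₖ)/6 ÷ 21 = Σ(y₁ₖ − y₀ₖ)/42, the crude difference. Zero cells do no harm. With unequal losses it can differ slightly from the crude value.

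**The case against.** The authors foresaw sparse SOC counts. The model is offered only when counts are not extreme, a stratified test is named for the other case, and pooling is something they may consider, with 0 or 1 as an example. Cut-offs and a companion estimate for CMH may stand in an analysis plan that is not shown. All this is fair: the identity-link model is not a fixed first choice and pooling is not a rule.

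The rates are also uncertain. They rest on 2/19 (exact 95% interval 1–33%) and 0/5 (upper limit 52%), so the figures for a true zero rate in trial 2 are a limiting case; the Protocol's own detectable difference assumes 10%. If NGOs do differ (an assumed log-odds SD of 0.5 or 1.0), collapse to one stratum at 10% v 42% falls to 33% or 19%. The seven-stratum boundary share stays at 97–98%.

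Three stronger readings are tempting and are not supported:

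- *No adjusted difference would remain.* Pooling leaves two or more strata with an interior fit in about 40–55% of trials at a 10–10.5% SOC rate. It fails outright only near 0%. The crude difference is always available.
- *The primary estimate would be picked after seeing the data.* With complete strata, the crude and Mantel-Haenszel estimates coincide. Mainly the interval and P-value are exposed.
- *Analyst blinding cannot be kept.* Coded arms still show counts per arm, which is enough to choose between the model and CMH. Only pooling needs the SOC arm identified, and the Protocol does not say who decides or when.

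**Conclusion.** The point holds in limited form and should be corrected. What the Protocol states, apart from any detail left to an analysis plan, fits its own design poorly. Adjustment for the randomization stratum is conditional on observed data, and the method follows outcome counts by arm. At the planned 10% SOC rate, a seven-stratum identity-link fit would be interior in only about 2–5% of trials. The pooling example flags about 6.2 of 7 NGOs. The fallback as written gives a P-value without the stated measure or an interval.

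These sizes assume six SOC men per NGO, no true NGO differences and SOC rates near 10%. At 20% the boundary share is about 70% and 4.6 NGOs are flagged. The pooling option and the statement that analysts are blinded need to be reconciled. That is a gap in the text, not proof that blinding would be lost.

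**What to change.** For both trials, state one primary analysis:

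- the Mantel-Haenszel risk difference stratified by all seven NGOs;
- a sparse-data interval (Sato variance or stratified Miettinen–Nurminen);
- the CMH P-value, in its exact form if needed.

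Delete the condition that NGO differences must first be seen, the identity-link option and the pooling option. With pooling gone, no step in the choice of method requires the SOC arm to be identified, which settles the tension with the blinding statement.

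The change costs wording only; the sample size is untouched. The one small loss is that the primary analysis has no covariate model.
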